# Introduction and study rationale

## Malaria and malaria control in Africa

Malaria remains the most important parasitic disease and is globally responsible for 300-500 million fever episodes and 1.5-2.7 million deaths per year (WHO 1997). The greatest burden of malaria is in sub-Saharan African (SSA) where it has been estimated that 40% of fever episodes are caused by malaria and where children regularly experience several malaria episodes a year (Brinkmann and Brinkmann 1991, Müller et al. 2001). Most malaria deaths occur in young children of rural SSA areas with little access to health services (WHO 1997, Greenwood et al. 1987, Snow et al. 1999, Müller et al. 2003).

In SSA, the basis of malaria control is early diagnosis and prompt treatment with effective antimalarial drugs. This strategy is now complicated through the increasing development of resistance by *Plasmodium falciparum* to existing and affordable first-line drugs such as chloroquine and sulphadoxine-pyrimethamine (Trapé 2001). Parasitological resistance to sulfadoxine-pyrimethamine has reached already 20-40% in parts of East Africa and increasing resistance has been described also for West Africa (Mockenhaupt et al. 2005). The situation is likely to become critical in a couple of years (White et al. 1999). If antimalarial multidrug resistance emerges in SSA at the speed observed in south-east Asia, the development of alternative drug regimens is of overriding public health importance.

Treating malaria with a combination of effective drugs is therefore becoming a new paradigm in malaria control, with the particular aim to delay and possibly reverse the development of drug resistance through different mechanisms (Nosten and Brasseur 2002). Artemisinin drugs in combination with a variety of partner drugs have proved highly effective in a number of field trials (International Artemisinin Study Group 2002). Although the costs for artemisinin combination therapy (ACT) are currently still higher than the price for chloroquine and pyrimethamine-sulfadoxine regimens, more and more African countries are currently switching their antimalarial first line treatment to ACT. So far no resistance to ACT has been described in vivo. Most research focuses on the use of artesunate combined with currently used standard drugs such as amodiaquine and sulphadoxine-pyrimethamine. There is evidence that combinations improve efficacy without increasing toxicity, however cure rates vary widely and depend on the level of resistance of the partner drug. New compounds with novel mechanisms of action and a short half-life to prevent resistance are therefore urgently needed to protect such ACT. The combination of the two short acting drugs methylene blue and artesunate or the combination of methylene blue with the long-acting and still sufficiently effective AQ ought to be considered as a possible solution to this problem in SSA (Akoachere et al. 2005, Barker et al. 2005).

## MB in the treatment of malaria

MB (Methylthioniniumchlorid) is a water-soluble dye used for a very long time in industry and medicine. In medicine, it can be administered both orally and parenterally. In humans, the drug is rapidly and widely distributed throughout the body (DiSanto and Wagner 1972). It is generally crossing the blood-brain barrier, but according to animal data i. v. administration initially seems to lead to much higher concentrations in the central nervous system than oral administration (Peter et al. 2000). The drug is well absorbed from the gastrointestinal tract, maximal plasma concentrations are reached after 1-2 hours following oral administration, and the plasma half-life is around 10-12h hours (own unpublished data). Renal excretion of MB is the main elimination pathway: 53-97% of an oral dose is excreted in unchanged or leuco-form in the urine over a 5 day period (DiSanto and Wagner 1972, Peter et al. 2000). In sheep, the 24 hours LD50 after a single i. v. MB administration was 42.3 mg/kg (95% CI: 37.3-47.9); methaemoglobin production was minimal with doses as high as 50 mg/kg, and no significant haematological changes were seen up to 4 weeks after a total dose of 30 mg/kg was administered i. v. over 18 hours (Burrows 1984). From this study it was concluded that the dosage of i. v. MB may safely be increased up to at least 15 mg/kg in the therapy of severe methaemoglobinaemia in humans. However, in one older publication i. v. doses of MB exceeding 7 mg/kg have been reported to cause distressing symptoms, such as restlessness, fine tremor, nausea and chest pain. Grayish blue discolouration of the skin, resembling cyanosis, but with normal values for pO2, and haemolytic anaemia was observed if i. v. doses of 15 mg/kg or more were given to children (Goluboff and Wheaton 1961). In these case reports no significant methaemoglobinaemia was observed. However, MB was well tolerated in oral doses of up to 17 g (5 x 100-200 mg per day) during initial observations in malaria therapy in adults (Guttmann and Ehrlich 1891). Moreover, no significant side effects besides some mild dysuria were reported during treatment of 40 young children, including infants, with malaria in Brasil with oral doses of 20-50 mg/kg/day MB over several days to weeks (Ferreira 1893). It thus appears as if MB given orally is safe even in higher doses compared to intravenous application. This idea is supported by some evidence for significant differences in organ distribution leading to major differences in pharmacokinetics between oral and intravenous MB administration (Peter et al. 2000). Finally, all persons taking MB develop blue urine over the following days.

MB has already been successfully used against malaria some 100 years ago (Guttmann and Ehrlich 1891, Ferreira 1893, Ehrlich 1913). Its further use against human malaria is not well documented, thus only observational data support its efficacy, particularly in malaria cases found refractory to quinine (Dale 1956). The drug was no longer used against human malaria after other effective and non-toxic drugs appeared on the market (e.g. CQ). However, MB has been shown to be the most effective of its analogues in inhibiting the growth of *P. falciparum* in culture, and its antimalarial efficacy in the mouse model is achieved at concentrations similar to the ones used in the treatment of methaemoglobinaemia in humans (Vennerstrom et al. 1995). MB appears to act similar to 4-aminoquinoline antimalarials by preventing the polymerization of heme, which is produced during the digestion of host cell cytosol in the parasite food vacuole, into hemozoin. In the past, the drug has also been used against gastrointestinal and urogenital infections and against rheumatism. MB is a registered drug in most countries for a number of still very relevant indications. It is mainly known for its efficacy in the treatment of methaemoglobinaemia both in adults and in children (e.g. intoxication with nitrite or a number of methemoglobin-inducing drugs), and for the treatment and prevention of ifosfamide-induced encephalopathy in cancer treatment. In the case of methaemoglobinaemia and for prevention of ifosfamide-induced encephalopathy, the dosage is 1-2 mg/kg i. v. 2-6 times per day (Mansuri and Lurie 1993, Küpfer et al. 1994, Zulian et al. 1995, Aeschlimann et al. 1998, Pelgrims et al. 2000). As methaemoglobin formation has been reported as a potential serious complication of falciparum malaria in Africa, the use of MB as an antimalarial may help to prevent tissue anoxia (Anstey et al. 1996). MB is furthermore locally used for diagnostic purposes, for photodynamic therapy in tumour treatment, against skin and mucosa infections, topically against ulcera (10% solution), and may be even be beneficial against sepsis (Orth et al. 1995, Galili et al. 1997).

The interest in MB as an antimalarial drug was reactivated when *P. falciparum* glutathione reductase was identified as a target of the drug in the parasite (Färber et al. 1998, Sarma et al. 2003, Schirmer et al. 2003). MB inhibits the glutathione reductase of *P. falciparum* but not the human glutathione reductase at therapeutically used concentrations (Böhme et al. 2000, Kanzok et al. 2000, Davioud-Charvet et al. 2003).

There was some evidence that MB, being a glutathione reductase inhibitor, might potentiate the activity of CQ or even reverse CQ resistance (Ginsburg 2002, Sarma et al. 2003). Therefore the safety and efficacy of MB against uncomplicated malaria in humans was first tested in the combination with CQ. This drug combination was found to be safe even in G6PD deficient adults and children (Mandi et al. 2005, Meissner et al. 2005). The combination was however not sufficiently effective against uncomplicated falciparum malaria in young children when given at a dose of 12 mg/kg over three days (Meissner et al. 2005). In a subsequent dose finding study in a comparable population of young children, a significantly better efficacy of MB against uncomplicated malaria was demonstrated when 3-6 times higher MB doses were given over three days (unpublished data). Although there was a significant reduction especially in early treatment failure rates, an unacceptable high rate of recrudescence most likely due to the high background resistance of the local parasites against CQ was observed.

Therefore the ideal partner drug to MB still needs to be identified. Two studies have recently shown a synergistic effect of the drugs MB and AS in vitro and in rhesus monkeys (Akoachere et al. 2005, Barker et al. 2005). As both drugs are short acting and no resistance has been demonstrated so far, AS-MB appears to be a promising drug combination. However, to be useful under real life conditions in SSA such a combination needs to be highly effective in a three days regimen. Monotherapy with AS for three days achieved only low cure rates (between 20% and 50% on day 28) in nonimmune populations outside SSA (Borrmann 2003). However, only few studies have studied the efficacy of shorter regimens of AS monotherapy in SSA. While five day regimens of AS monotherapy reached rather high cure rates in semiimmune populations of Tanzania and Nigeria, a three days regimen conducted in 50 children aged 4-15 years with uncomplicated malaria in a hyperendemic area of Gabon had cured only 72% of children by day 28 (Borrmann 2003). However, in this study, the day 14 cure rate was still 92% and children developed mainly asymptomatic parasitaemia afterwards.

AQ alone has been shown to be still sufficiently effective in many areas of SSA where chloroquine is failing (Müller et al. 1996, Greenwood et al. 2005). The combination of AS-AQ has been shown to be highly effective in SSA (International Artemisinin Study Group 2002). AS-AQ together with artemether-lumefantrine have been chosen as the two new official first-line treatments of uncomplicated malaria in Burkina Faso since the year 2006. Thus, comparing the two MB-based combinations MB-AS and MB-AQ with the standard of care AS-AQ is important to judge the safety of these regimens in Burkina Faso and to provide first data on the comparable efficacy.

With effect of May 2006, the World Health Organisation has officially recommended to no longer using malaria monotherapy in the treatment of uncomplicated falciparum malaria (Nelson 2006).

# Trial objectives and purpose

The purpose of the study is to investigate the safety and efficacy profile of the combinations MB-AS and MB-AQ in comparison with AS-AQ in African children with uncomplicated falciparum malaria.

The primary objective of this study is:

- To investigate the safety of the combinations MB-AS and MB-AQ in children with uncomplicated malaria caused by *Plasmodium falciparum*

Justification: MB, AS, AQ and AS-AQ have been shown to be safe in the target population. However, to treat children with the combination of MB-AS or MB-AQ is new. Thus, all adverse events of these new combinations are of interest. The comparison with AS-AQ, the new official first-line treatment for uncomplicated malaria in Burkina Faso, will help to judge the safety of MB-AS and MB-AQ in the study population. This trial should give the necessary information about the safety of the combination MB-AS and/or MB-AQ for judgment and planning of future phase III trials.

The secondary objective of this study is:

- To investigate the efficacy of MB-AS and MB-AQ

Justification: The combination MB-chloroquine has been shown to be effective against malaria in the Nouna study population. However a high rate of recrudescences was observed due to high background resistance to CQ (Meissner, unpublished). Therefore alternative drug combinations with MB need to be identified. There is now sufficient evidence from in vitro and animal models for existence of synergy between the two short acting drugs MB and AS (Akoachere et al. 2005, Barker et al. 2005). Thus AS seems to be an ideal partner drug to MB but it remains to be shown that MB-AS is sufficiently safe and effective when given over a period of three days. Alternatively, the combination MB-AQ could still be sufficiently effective even in areas of high resistance against chloroquine. This trial should give the necessary information about the efficacy of the combinations MB-AS and MB-AQ for judgment and planning of future phase III trials.

# Definition of outcomes

Primary endpoint:

- Incidence of observed and self-reported non-serious adverse events over the 28 days observation period (definition chapter 11)

Secondary endpoints:

- Incidence of serious adverse events (definition: chapter 11) over the 28 days observation period
- ACPR rate until D28
- Early treatment failure (ETF) rate
- Late clinical failure (LCF) rate at D14 and D28
- Late parasitological failure (LPF) rate at D14 and D28
- Fever clearance time
- Parasite clearance time
- Change in haematocrit after 2, 3, 7, 14 and 28 days compared to baseline

*Justification:* SAE rates and clinical and parasitological failure rates as well as fever and parasite clearance times are standard endpoints to judge the safety and efficacy of antimalarial drugs. This information will be relevant to plan future phase III trials.

# Design of the trial

Single-centre, randomized, controlled phase II trial in children aged 3-4 years with uncomplicated falciparum malaria.

Randomisation and blinding

After creation of computer generated envelopes, 180 children aged 3-4 years with uncomplicated falciparum malaria will be randomized to one of the three treatment groups: MB-AS (3 day regimen), MB-AQ (3 day regimen), AS-AQ (3 day regimen).

Due to the coloration of urine through MB, blinding of patients will not be possible. However, all lab technicians examining the blood samples for malaria parasites and other study relevant aspects will be blinded to treatment regimen.

Duration of the trial

The study will become implemented between July and October 2006.

# Selection and withdrawal of subjects

Sample size

180 children (60 children in each of the three different treatment regimens) will be enrolled into the study. The sample size of 60 per arm enables us to demonstrate a difference in AE rates of 10 % with 90% power and at a 0.05 significance level.

Inclusion criteria

- 3-4 year (36-59 months) old children
- Between 10 kg and 22.5 kg body weight
- Ability to swallow tablets
- Uncomplicated malaria caused by *P. falciparum*
- Asexual parasites ≥ 2000/µl and ≤ 200000/µl
- Axillary temperature ≥ 37.5°C
- Burkinabe nationality
- Informed consent

Exclusion criteria

- Complicated or severe malaria
- Any apparent significant disease
- Anaemia (haematocrit < 21%)
- Treated in the same trial before
- Antimalarial treatment prior to inclusion (last three days), except children having been treated with chloroquine

Withdrawal criteria

Participants may be withdrawn from the study at their guardians request and any change in the patient’s condition which in the investigator’s opinion, for reasons of safety or ethics, precludes further participation in the trial. In case of vomiting after the repeated drug intake (one repetition only) of the first drug ingestion, the participant will be withdrawn from the study. Subjects withdrawn from the study during the first 3 days will be replaced.

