# Statistics

Sample size calculation

When the sample size in each group is 54, a 5% level Chisquare test will have 80% power to detect a difference in proportions by a variance of proportions of 0,009 and an average proportion of 0.183. This szenario is met by the assumption that the rate of adverse events is 25% in the AQ+AS group as well as in the AQ +MB group, and 5% in the AS+MB group.

After a global Chisquare test for the Nullhypothesis "No difference between the three treatment groups" pairwise differences between groups will be tested by two group Chisquare tests. All 4 tests are on the 5% level and no adjustment of the significance level is needed because of the closed testing principle. On closed testing procedures with special reference to ordered analysis of variance. 95% confidence intervals will be calculated for the AE rates. Descriptive statistics will use minimum, 25% quantile, mean, median, 75% quantile, maximum für continuos values and tabulation for categorical values.

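### The selection section claims 90% power for a 10% difference in AE rates with 60 per arm; this contradicts the Statistics section and is wrong at the AE rates the protocol assumes

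*Protocol*

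**What the plan says.** The protocol justifies its sample size in two places.

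- **Selection and withdrawal of subjects, Sample size.** The trial size is fixed: "180 children (60 children in each of the three different treatment regimens) will be enrolled into the study". The justification follows: "The sample size of 60 per arm enables us to demonstrate a difference in AE rates of 10 % with 90% power", at a 0.05 significance level. No base rate, test or sidedness is given.
- **Statistics, Sample size calculation.** Here the protocol gives other figures: "When the sample size in each group is 54, a 5% level Chisquare test will have 80% power to detect a difference in proportions", specified by a "variance of proportions of 0,009 and an average proportion of 0.183". The rates behind these inputs are "25% in the AQ+AS group as well as in the AQ +MB group, and 5% in the AS+MB group". The three-group chi-square test comes first and two-group chi-square tests follow, all at the 5% level under the closed testing principle.

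Both statements concern adverse event rates, the primary endpoint.

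**The concern.** The two justifications cannot both describe the same design. One gives 60 per arm, 90% power and a 10% difference. The other gives 54 per group, 80% power and a largest difference of 20 points. Halving the difference to be detected normally needs roughly four times the patients at similar rates, so higher power for half the difference from six more children per arm is implausible on its face.

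Safety is the primary objective, and the protocol wants the results to inform phase III planning. Ethics committees or planners who rely on the selection section would credit the trial with a sensitivity to AE differences that it does not have.

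**Working it through.** **Inputs.** 60 per arm, 1:1:1, 10% difference and alpha 0.05 (Selection and withdrawal of subjects); 54 per group, 80% power, rates 25%, 25% and 5%, global then pairwise chi-square tests (Statistics). Assumptions: two-sided testing, since sidedness is not stated, and a 10% difference read as 10 percentage points.

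**Step 1: reproduce the Statistics figure.**
- Mean rate: (0.25 + 0.25 + 0.05)/3 = 0.1833.
- Variance of the rates: (0.0667² + 0.0667² + 0.1333²)/3 = 0.00889. Both match the protocol after rounding.
- Noncentrality: λ = n × 3 × V / [p̄(1 − p̄)].
- At n = 54: 54 × 3 × 0.00889/(0.1833 × 0.8167) = 9.62. On 2 df this gives 79.9% power (80.5% with the protocol's rounded inputs).
- At n = 60: λ = 10.69 and power is 84% (85% with rounded inputs).

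The Statistics calculation therefore holds. Simulating the global test gives higher values, 88% at 54 and 92% at 60, so the formula is conservative here.

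**Step 2: test the 10%/90% claim.** For a two-group chi-square test,

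power = Φ{ [ |p1 − p2|√n − 1.960 √(2p̄(1 − p̄)) ] / √(p1(1 − p1) + p2(1 − p2)) }.

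With n = 60, √n = 7.746, so a 10-point difference gives a first term of 0.775.
- 25% v 15%: (0.775 − 1.960 × 0.566)/0.561 = −0.595.
- 15% v 5%: (0.775 − 1.960 × 0.424)/0.418 = −0.136.
- 25% v 35%: (0.775 − 1.960 × 0.648)/0.644 = −0.769.

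| Rates | Power, formula | Power, exact enumeration | n per arm for 90% |
|---|---|---|---|
| 25% v 15% | 28% | 28% | 335 |
| 15% v 5% | 45% | 46% | 188 |
| 25% v 35% | 22% | 23% | 440 |

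**Step 3: apply the planned test order.** Pairs are tested after the global test. Simulating both steps at 60 per arm, with the third arm at the first rate of each pair, gives about 19% (25% v 15%), 33% (15% v 5%) and 16% (25% v 35%). These depend on the third arm: 15%, 5% and 5% gives about 40% for the 15% v 5% pair.

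**Step 4: look for a reading that yields 90%.**
- One-sided 5% test: 39% (25% v 15%) or 57% (15% v 5%).
- Relative 10% reading, 25% v 22.5%: about 5%.
- Global test with a 10-point spread: 26% (25/25/15%) or 40% (15/15/5%).
- An arm at exactly 0%: 10% v 0% gives 72% by formula and 86% exact, two-sided; 95% exact, one-sided. The global test at 10/0/0% gives 89% by formula and 95% by simulation. An AE rate of 100% in an arm mirrors the two-group result.
- A 20-point difference, 25% v 5%: (1.549 − 1.960 × 0.505)/0.485 = 1.154, so 88% (exact 90%).

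Only the degenerate cases reach about 90% for 10 points. The pairwise 25% v 5% comparison does give roughly 90%, but for a 20-point difference.

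**The case against.** The selection sentence names no base rate and no test, so it is too strong to say that no AE rates could make it true. At 10%, 0% and 0% the global test has 89% to 95% power. That stands as a limit on the wording, but it does not rescue the sentence: the protocol assumes rates of 5% to 25%, not an arm without adverse events.

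A reader might infer that the trial is underpowered for its own scenario. It is not. The stated 80% belongs to 54 per group; at the planned 60 the same method gives about 84%, and the pairwise 25% v 5% test about 88-90%. The 90% is thus close to right for a 20-point difference, and the effect size may be what went wrong in the sentence. The document does not say.

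A reader might also infer that the protocol would treat a non-significant test as proof of equal safety, or that it should report intervals for the arm differences. It claims no such proof. It promises "95% confidence intervals will be calculated for the AE rates", and intervals for differences could be specified in a statistical analysis plan that is not at hand, so their absence is no fault here.

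Finally, the correction changes neither enrolment nor the tests. That is so, but the stated power for the primary endpoint is still false.

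**Conclusion.** The power statement in the selection section is wrong as written. It contradicts the Statistics section on group size, power and effect size, and it fails at the AE rates the protocol assumes. Against the stated 90%, two-sided pairwise power for 10 points at 60 per arm is about 28% (25% v 15%), 46% (15% v 5%) or 22-23% (an increase from the comparator's 25% to 35%). It is about 19%, 33% and 16% respectively once the global test must first be significant.

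These figures assume two-sided 5% tests without continuity correction and 60 children analysed per arm; the lower set also assumes the third arm is at the first rate of each pair. A one-sided or relative reading does not restore the claim. The Statistics calculation is sound and needs no correction.

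**What to change.** Delete the 10%/90% sentence under Selection and withdrawal of subjects and replace it with one consistent with the Statistics section, for example:

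*With 54 per group, the three-group chi-square test has 80% power if AE rates are 25%, 25% and 5%. With the planned 60 per group, the same method gives about 84% (about 88-90% for the pairwise 25% v 5% comparison). Power for a 10-point difference is well below this: pairwise, before the requirement of a significant global test, about 28% for 25% v 15%, 46% for 15% v 5% and 22-23% for 25% v 35%.*

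Do not describe the 54 as evaluable children. The protocol states no attrition assumption linking 54 to 60; it says only that withdrawals in the first 3 days are replaced.

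Optionally, 95% confidence intervals for the arm differences in AE rate can be reported alongside the planned tests, without replacing the primary analysis.

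The cost is one changed passage, submitted as an amendment if the protocol is already approved, and a less favourable stated power. Enrolment, randomisation and the planned tests stay as they are.
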